### Study activities and interventions

ASCOT study activities can be broadly divided into: pilot trial activities and interventions with recruited people with TB and their households, which will gather data to support process evaluation; and complementary enhanced process evaluation activities with a subset of people with TB and key multisectoral stakeholders. 

**
*Pilot trial*
**

*Recruitment of people with TB and their households*

The ASCOT team will support BNMT DPCs, CHS, and FCHVs to recruit 128 people with TB across study sites. Participants will be identified prospectively during the recruitment period once they are diagnosed and notified to the NTP register. Participants will be invited to participate at their initial TB clinic visit, usually prior to initiation of treatment. They will then be randomised to a study arm at that clinic visit.

Household contacts of participants in social and socioeconomic study arms will be invited to participate in the social support activities using index-patient initiated invitations, which has been reported to be a preferred recruitment method for household studies in multiple settings
^
34–
36
^. Specifically, people with TB recruited to the study and randomised to the social or socioeconomic arms will be given an information leaflet and advised to inform their household members about the social support activities. As per WHO guidance, a household contact will be defined as “a person who shared the same enclosed living space for one or more nights or spent frequent or extended periods during the day with the index case during the 3 months prior to commencement of the current treatment episode”
^
37
^. Household contacts will also be given a separate PIS and asked to complete separate consent forms.

Participants will be free to withdraw from the study at any time by indicating this desire verbally and/or in writing to a member of the project team. Individual-level data from participants who withdraw will not be used further and will be securely deleted from project records. Deidentified group-level data collected during activities such as Focus Group Discussions, in which a participant who later withdraws from the study took part, will remain available for analysis.

*Household visits and surveys*

All participants will receive a household visit at three time points to complete the ASCOT survey:

**Visit one:** two to four weeks after TB treatment initiation, during the “intensive treatment phase”;

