**Figure 7. f7:**
[figure not shown]
Intervention activities conducted in each study arm. Abbreviations: ASCOT = the “Addressing the Social Determinants and Consequences of Tuberculosis” project; IEC = Information, Education, and Counselling; NTCC = Nepal National Tuberculosis Control Centre; TB = tuberculosis; UCT = unconditional cash transfer.

Following refinements by BNMT team and TSC inputs, recruitment will proceed. Again, when a study site reaches 32 recruited participants, recruitment will discontinue in that district. This provides ample allowance for completion of intervention activities and three surveys in 32 participants given the predicted attrition rate of ≤10% in the study sites.

The longitudinal survey data detailing participant feedback will form part of the process evaluation of the acceptability and feasibility of the ASCOT intervention. This will be supplemented by real-time self-reported ASCOT project feedback, and time and expense diaries of BNMT implementers, including DPCs and CHS. This data will be further complemented by the enhanced process evaluation aiming to evaluate health systems readiness and scalability of the ASCOT intervention. 

There will be multiple opportunities during the implementation of the pilot trial to assess for any harms or adverse effects. First, the longitudinal survey includes questions related to feedback from participants on the interventions received and involvement in the ASCOT project. Second, after each TB Club is conducted, participants will be asked to provide verbal and written feedback on the activities undertaken during the TB Club, including whether they perceive any of the activities to have caused harm or have the potential to cause harm. Third, issues relating to harm or adverse effects of the ASCOT project are included in the topic guides for KIIs and FGDs. All of these data will be analysed in real-time during the project and discussed between the ASCOT project team and where necessary the TSC to identify if any remediating actions are required. The criteria for discontinuing interventions include: participants who withdraw from the ASCOT project who, as an individual and inclusive of their household, will no longer receive the intervention; harm or adverse effect is identified that is felt by the project team and TSC to preclude continuation of interventions; and acts of God or unforeseen cuts to the study budget curtailing project activities.

**

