### Outcomes to be measured

**
*Co-primary outcomes*
**

The co-primary outcomes of the ASCOT pilot trial are acceptability and feasibility of the social, economic, and socioeconomic support interventions.

*Feasibility* will be measured using quantitative data including:

i) Recruitment (e.g. number of people invited, recruited, and participant attrition);ii) Fidelity to survey completion and the intervention (e.g. adherence to and completion of socioeconomic support delivery including receipt of cash transfers and attendance at TB Club amongst intervention arm participants); andiii) ASCOT staff time and costs plus overall project costs.

*Acceptability* will be measured using mixed-methods including:

i) Quantitative analysis of the implementer and participant satisfaction form;iii) Thematic analysis of the qualitative FGD and KII data within Sekhon’s Framework for healthcare interventions and quantitative analysis of the brief questionnaire completed prior to FGDs will include evaluation of health systems readiness and scalability
^
50,
51
^.

**
*Secondary outcomes*
**

Unpowered, exploratory secondary outcomes will compare the proportion of people with TB in each study arm by rates of:

*TB treatment success:* NTP-defined outcome of completed TB treatment or confirmed cured documented in TB register.
*Catastrophic costs:* TB-affected households that incur total out-of-pocket expenses and lost income during TB illness that equated to more than 20% of the same household’s annual pre-TB income.
*Wellbeing:* measured by self-reported levels of stigma, depression, and quality of life at six-month follow-up adjusted for baseline.

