### Data analysis and statistical plan

**Co-primary outcome analyses**

**
*Feasibility*
**

Target versus observed participant recruitment, completed cash transfers, completed TB Club attendance, and attrition from follow-up at each survey time point will be reported across study arms using the CONSORT flow diagram, summarised using proportions and percentage rates, and where relevant compared across study arms using a Chi-2 test with p values of <0.05 considered significant.

ASCOT staff and project costs will be summated for the project as a whole and also as total and mean costs by specific project activities (i.e. TB Clubs, home visits, cash transfers). The latter will support generation of estimates of the costs to deliver a single unit activity such as a TB Club or Cash Transfer. Continuous costs data will be summarised by median with interquartile range or mean with standard deviation depending on the distribution of the data. Total ASCOT staff and project costs will be compared across study arms using the Kruskal Wallis test or one way ANOVA with p values of <0.05 considered significant.

**
*Acceptability*
**

Quantitative data from implementer and participant feedback forms detail the respondents’ ratings on the provision of ASCOT project activities received including recruitment, TB information and education, home visit, TB club, and cash transfers. Responses are provided in 5-point Likert Scale including 1 “Very bad”, 2 “Bad”, 3 “Neither good nor bad”, 4 “Good”, and 5 “Very Good”. Responses will be summarised using proportions and rates of response by category. Proportions of respondents reporting “Good” and “Very good” in each category will be aggregated and compared across study arms where relevant using a Chi-2 test with p values of <0.05 considered significant.

Qualitative data will be analysed by applying thematic analysis within Sekhon’s framework of healthcare interventions
^
51
^ and also application to the NoMAD tool’s
^
49
^ four constructs (coherence, engagement, collective action, and reflexive monitoring) using NVivo 12 to manage the data
^
52

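### The article calls each between-arm comparison of the co-primary outcomes significant at p<0.05, about ten tests with no exploratory label, so a false difference has roughly a 20-40% chance of appearing somewhere.

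*Protocol article*

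**What the plan says.** Outcomes to be measured makes feasibility and acceptability of the three forms of support the co-primary outcomes. The analysis rule is in Data analysis and statistical plan, Co-primary outcome analyses.

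- **Acceptability.** Ratings on a five-point scale are collected for activities "including recruitment, TB information and education, home visit, TB club, and cash transfers". The top two categories are pooled, and the resulting proportions "will be aggregated and compared across study arms where relevant using a Chi-2 test with p values of <0.05 considered significant".
- **Feasibility.** The measures are "Target versus observed participant recruitment, completed cash transfers, completed TB Club attendance, and attrition from follow-up at each survey time point". They are summarised as proportions and "where relevant compared across study arms using a Chi-2 test with p values of <0.05 considered significant". Total staff and project costs are also compared across arms, by Kruskal-Wallis or ANOVA, at the same threshold. The cost test does not carry the qualifier about relevance.
- **Visits.** Study activities and interventions says: "All participants will receive a household visit at three time points to complete the ASCOT survey". Under Study arms and activities: "The longitudinal survey data detailing participant feedback will form part of the process evaluation of the acceptability and feasibility".
- **Contrast.** For the secondary outcomes, Outcomes to be measured says: "Unpowered, exploratory secondary outcomes will compare the proportion of people with TB in each study arm". The co-primary analyses carry no such label.

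Sample size and statistical power justifies the numbers by general recommendations for pilot studies and for TB cost surveys. It gives no effect size or power for a comparison between arms.

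**The concern.** The article applies the full 0.05 threshold separately to every co-primary comparison and says that a result below it counts as significant. With about ten such tests and no limit on the family, the chance that at least one crosses the threshold when the arms do not differ is several times 0.05. Nothing in the section tells a reader to treat such a result with caution, whereas the secondary outcomes do carry that warning.

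The pilot is meant to inform the large trial (Secondary aims), and its preliminary findings go to a stakeholder workshop that recommends refinements to the intervention (Workshop and dissemination meeting). A chance difference in, say, home-visit ratings, reported as a significant co-primary result, would enter both without a caveat. With 32 people per arm, a non-significant result is equally open to misreading as evidence that the forms of support are equivalent.

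**Working it through.** **1. The stated sample size.** 4 arms x 32 = 128, as the article gives. The aim is 100 people with complete data, which allows a loss of 1 - 100/128 = 21.9%. This reproduces, but no between-arm power stands behind it.

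**2. Counting the tests.**
- Ratings: 5 activities, counted once each.
- Cash transfers: 1. TB Club attendance: 1.
- Attrition: 3, one per survey time point.
- Total: 5 + 1 + 1 + 3 = 10 tests, from 5 + 1 + 1 + 1 = 8 measures. The cost comparison makes 11 tests and 9 measures.

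Recruitment appears in the feasibility list but is not counted. Randomisation follows consent and recruitment, and the blocks fix the arm totals, so it cannot be compared by arm. The cost test is left out of the main figure because costs differ between arms by design.

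**3. Nominal family-wise rate.** For k independent tests at 0.05, the chance of at least one false positive is 1 - 0.95^k.

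| k | What is tested | Rate |
|---|---|---|
| 5 | ratings only | 0.226 |
| 10 | list above | 0.401 |
| 11 | with costs | 0.431 |

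**4. Correlation.** The tests share participants, so they are probably positively correlated. The size of the correlation is not in the article and is assumed. For ten equicorrelated tests on 3 degrees of freedom the rate is 0.36 at 0.3, 0.30 at 0.5 and 0.18 at 0.8.

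**5. Actual size of the Chi-2 tests.** With 32 per arm and rates near 0 or 1 the test is often conservative. Ratings of recruitment, education and home visits compare four arms. The TB Club and cash-transfer ratings, and the two completion measures, compare only the two arms that receive each component. Simulated size per test:

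| Favourable rate (assumed) | Four arms | Two arms |
|---|---|---|
| 80% | 0.0488 | 0.0510 |
| 90% | 0.0416 | 0.0562 |
| 95% | 0.0334 | 0.0322 |

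Attrition is cumulative, so its three tests overlap. With 5-10% total loss accruing evenly over the three visits (assumed), the chance of any false positive among them is 0.06-0.08, not the 1 - 0.95^3 = 0.14 of independent tests at full size.

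Combining three four-arm tests, four two-arm tests and the attrition set as if independent of one another:
- 95% favourable, attrition 0.06: 1 - (0.9666^3 x 0.9678^4 x 0.94) = 0.26.
- 80% favourable, attrition 0.08: 1 - (0.9512^3 x 0.9490^4 x 0.92) = 0.36.

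A direct simulation of the ten tests over these rates gives 0.22-0.36. Within-person correlation lowers the rate.

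**6. If ratings were tested at each visit.** This adds ten tests. For 20 tests the rate is 0.64 if independent, 0.42 at correlation 0.5 and 0.22 at 0.8. The article neither states nor rules out such testing: in the analysis section, only attrition is tied to each time point.

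**The case against.** Several points on the other side are sound.

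- **The qualifier.** The proportion tests apply only where relevant, so not every comparison need be run. That is true, but the qualifier sets no limit and does not change how a result below 0.05 is described. Five rating tests alone give 0.13-0.23 over correlations from 0.8 to 0.
- **A confirmatory reading.** A reader might infer that the co-primary tests are confirmatory because only the secondary outcomes are called exploratory. The article does not support this. It uses the same 0.05 wording for the analyses headed secondary exploratory, and it leaves effectiveness to a later, well-powered trial. The defect is the missing label, not a declared confirmatory claim.
- **Arms dropped on a p-value.** A reader might infer that a form of support will be selected or dropped on these tests. No passage says so. Acceptability also rests on thematic analysis, early adaptation follows a review of a few households per site discussed with the TSC, and refinements for the next trial come from a workshop.
- **A chance finding is more likely than not.** The stated list does not support this. The rate passes one half only from 14 independent tests, for example if ratings were also tested at each visit with low correlation.
- **Condensed article.** A headline measure, deciding visit or hierarchy may stand in the full protocol or an analysis plan, neither of which is shown. Their absence is therefore not a finding. The significance rule, however, is stated in the article itself.

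**Conclusion.** The point holds in limited form. The article attaches a significance claim at 0.05 to about ten co-primary comparisons that the sample was not sized to support, and it does not call them exploratory. If the arms are identical, the chance of at least one such claim is roughly 20-40%, against the nominal 5%: 0.40 if the ten tests are independent and at nominal size, and 0.22-0.36 in simulated Chi-2 tests with 32 per arm. Very strong correlation (0.8) between tests at nominal size takes it slightly below that range, to 0.18.

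These figures rest on assumed favourable rates of 80-95%, attrition of 5-10% and an assumed range of correlation. The article's own attrition expectations are below 5% in one place and at most 10% in another. The consequence is a risk of misreporting in a pilot whose results shape a later trial, not a breach of any stated decision rule. The change is worth making but does not threaten the design.

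**What to change.** In Co-primary outcome analyses:

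1. Delete the 0.05 significance threshold from the feasibility, cost and acceptability paragraphs.
2. State that feasibility and acceptability are judged on arm-specific proportions with 95% confidence intervals, and costs on summary estimates with 95% confidence intervals, alongside the qualitative findings.
3. Add that any between-arm comparison is exploratory, is not adjusted for multiplicity, and is not by itself a basis for preferring or dropping a form of support. This gives the co-primary comparisons the caution already given to the secondary outcomes.

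Two additions are optional: naming one headline acceptability measure and visit, and, if formal tests are kept, a Holm adjustment across the family. For ten tests, Holm judges the smallest p-value against 0.05/10 = 0.005 and costs power.

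The cost is wording only, with no new data or visits. The downside is that fewer results can be called significant.

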**Secondary exploratory outcomes analyses**

Key quantitative survey data will include TB-related costs, stigma, mental health, and quality of life. This will be supplemented by TB treatment outcome data from the National TB Program register.

As per our related research, WHO TB Patient Costs Survey methods will be used to calculate total direct costs, lost income, and catastrophic costs (total TB-related costs of more than 20% of the same household’s annual pre-TB income)
^
38
^. TB treatment outcomes will be collated from National TB Program registers and will be aggregated to TB treatment success (the sum of the National TB Program defined outcomes of “Treatment completion” and “Cure”) vs no TB treatment success (the sum of all other National TB Program defined outcomes including “Lost to follow-up”, “Death”, “Treatment Failure”, “No evaluation”, “Change to drug-resistant TB regimen” and “Transferred out”).

Stigma will be measured by locally developing stigma score for the Nepali context by adapting elements of the validated Van Rie stigma scale, which comprises ten stigma-related questions with 5-point Likert scale responses. Each response category of the scale will be assigned scores of: -2: strongly disagree, -1: disagree; 0: neither agree nor disagree; +1: agree, and +2: strongly agree. The total scores will range from -20 (no stigma) to +20 (highest levels of stigma). A threshold of equal or above the median cohort stigma score will also be used as a binary classification of stigma.

Mental health will be measured using an adapted version of the Patient Health Questionnaires, PHQ-9, which has been validated in Nepal. The tool explores anxiety, depression, wellbeing, and discrimination through nine questions with four-point scale responses of 0: not at all, 1: sometimes, 2: usually, and 3: always. The range of scores is from 0 to 27 and the following categorisations have been used in the validated tool: 1–4 minimal, 5–9 mild, 10–14 moderate, 15–19 moderately severe, and 20–24 severe depression level. A threshold score of equal or above 10 will also be used as a binary classification of depression.

Quality of life will be assessed using the EQ-5D-5L index. EQ-5D-5L uses five dimensions of quality of life: mobility, self-care, usual activities, pain or discomfort, and anxiety or depression. Each question includes a five-category response scale from 1: no problem, 2: slight problem. 3: moderate problem, 4: severe problems, 5: being unable. The EQ-5D-5L has not been validated in Nepal but has been validated in neighbouring India. Since Nepal and India share common sociocultural conditions and geographical features, we will calculated quality of life scores from the Nepal data using the validated value sets and weightings from India as estimates. The EQ-5D-5L also includes a health rating covariate measured on a scale of 0 to 100 based on participants' self-reporting. The participants are asked to choose an appropriate point that best defines their health condition for that day and to label it with a mark on the scale printed in the survey with 0 indicating lowest/poorest health and 100 indicating highest/best health.

Descriptive statistics will be used to analyse the quantitative survey data collected during household visits. In line with our own and others’ related research, the arithmetic means and 95% confidence intervals of patient costs data that is continuous in distribution will be described regardless of the distribution of the data, and any direct expenses, lost income, or annual income recorded as “zero” or missing will be replaced with the mean cost of each costs category (unless >10% of data for a particular variable is missing)
^
5,
6,
53
^. Nepalese rupees, the local currency, will be converted to United States Dollars according to
OANDA rates at the time of data collection. Continuous stigma and quality of life data will be summarised by median and IQR or mean and SD depending on distribution. Categorical data will be summarised as proportions with 95% confidence intervals. Continuous data relating to costs, stigma, mental health, and quality of life scores (including self-rated health) will be compared across study arms where relevant using the Kruskal-Wallis test or one way ANOVA with p values <0.05 considered significant. Proportions of participants above and below the binary thresholds of treatment success, catastrophic costs, stigma, and depression will be summarised and compared across study arms where relevant using a Chi-2 test with p values of <0.05 considered significant.

Statistical analysis will be done using STATA v15 (Statacorp, TX, USA).

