^. The Seed Award research used mixed methods to characterise the socioeconomic impact and barriers to accessing TB diagnosis and care in Nepal and to support design of potential interventions to overcome these issues
^
12
^. The Seed Award was housed within the “
IMPACT-TB” active-case finding study in Vietnam and Nepal (EU-Horizon 2020, grant 733174).

Both the Seed Award and IMPACT-TB were implemented by a well-established Nepalese NGO, Birat Nepal Medical Trust (
BNMT), with over 50 years of experience in implementing public health interventions in Nepal. IMPACT-TB and the Wellcome Seed Award research found that catastrophic costs were experienced by 61% of TB-affected households
^
13
^ and identified distinct socioeconomic factors impeding access to TB services (
Figure 1)
^
14
^. Focus group discussions (FGDs) characterised where along the patient pathway from TB symptoms to care seeking, diagnosis, treatment, and treatment outcome, support interventions could be delivered (
Figure 2). The research also demonstrated that people with TB in Nepal commonly experienced self-stigma
^
15
^ and exploratory analyses suggested that experiencing stigma was associated with catastrophic costs and worse TB treatment outcomes
^
16
^.

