### Study setting

Nepal is a lower middle-income country with a TB incidence of 245/100,000 people per year
^
23
^. Moreover, TB is the seventh leading cause of death in Nepal
^
24
^. Multi-drug resistance (MDR) rates are low in new cases but affect approximately 1 in 7 people being retreated for TB. Rates of treatment success are over 90% but lower for people with MDR-TB (70%) and very low for people with HIV-TB co-infection (9%). Treatment coverage is 70% indicating difficulties with access to TB services. This is compounded by stigma and discrimination towards people with TB and self-stigmatisation, which have been found to be prevalent in cohort studies in Nepal
^
14,
15,
25
^.

The National Tuberculosis Program (NTP) strategy focuses on a biomedical approach to address TB, including recent advances in expanded access to molecular diagnostic tests such as Xpert MTB/RIF
^®^
^
24
^. Nevertheless, despite free basic TB diagnostic tests and medicines and financial support for people with MDR-TB, more than half of TB-affected people experience catastrophic costs (defined as total TB-related costs and lost income >20% of a household’s annual income) of TB illness and care seeking in Nepal. Such costs include travel for Directly Observed Therapy (DOT), expenses for additional nutrition, and loss of income, and can lead to lower rates of TB treatment success, especially amongst underserved households
^
13,
25–
27
^. To address this, Objective 1 of the Ministry of Health and Population National TB Control Centre’s National Strategic Plan to End Tuberculosis in Nepal, 2021–2026 is “to strengthen the health system and improve quality TB services under universal health coverage and ensure no TB-affected family faces catastrophic costs due to TB by 2025”.

Fewer than one in two people in Nepal are covered by a basic social protection floor and one in four live in poverty
^
28
^. Despite widespread use of DOT, greater GeneXpert coverage, and intensified case finding, TB services in Nepal are challenged by significant geographical barriers, including mountains, flooding, landslides, and poor road infrastructure, all of which can hamper TB prevention and treatment outcomes
^
24,
26–
29
^. The Nepal NTP provides 3,000 Nepalese Rupees (~27 USD) monthly cash transfers to people with MDR-TB receiving ambulatory care, nominally for nutrition and transport
^
24
^. People with drug-sensitive TB (DS-TB) do not currently receive any financial support in Nepal
^
11
^.

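### Recorded zeros in patient costs, lost income and annual income are overwritten with a mean, which inflates mean costs and misclassifies catastrophic costs in both directions

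*Protocol article*

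**What the plan says.** The rule is in the protocol article, under the secondary exploratory outcomes analyses. Its scope is "any direct expenses, lost income, or annual income recorded as “zero” or missing", and the replacement is stated in the same sentence: "annual income recorded as “zero” or missing will be replaced with the mean cost of each costs category". The one exception is "unless >10% of data for a particular variable is missing". The only support given is consistency with related research by the team and others.

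The same variables build the catastrophic-cost outcome. The outcomes section counts "TB-affected households that incur total out-of-pocket expenses and lost income during TB illness", and the analysis section sets the threshold as "total TB-related costs of more than 20% of the same household’s annual pre-TB income". Continuous costs are then compared across arms by Kruskal-Wallis or one-way ANOVA, and the catastrophic-cost proportion by a chi-squared test, all at p<0.05. The outcomes section describes these secondary outcomes as unpowered and exploratory.

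**The concern.** Zero is listed beside missing as a separate trigger, so a recorded zero is overwritten by design. Nothing in the article separates a true zero from a blank entered as zero. Yet true zeros are plausible: the study-setting section notes that catastrophic costs occur "despite free basic TB diagnostic tests and medicines and financial support for people with MDR-TB", so some direct-expense items can cost nothing, and a person who kept working has no lost income.

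Three things follow.

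- Mean costs, the chosen summary measure, are too high.
- Households can cross the 20% line because of spending or losses that never happened, while a household with no income is given an average income and can drop below the line.
- If one arm has more true zeros than another, that contrast is part of what the trial observes, and the rule partly or wholly removes it.

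The rule is also incomplete. A mean cost is not defined for annual income, which is not a cost, and the text does not say whether the mean includes zeros or is taken within or across arms.

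**Working it through.** The article reports no figure that results from this rule, so there is nothing to reproduce. The effect can be derived from the rule itself. Zero shares, means and distributions below are assumptions.

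**1. Mean cost in one group.** Let z be the share of true zeros and m the mean among non-zero values.

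- True mean: (1-z)m.
- Zeros replaced by the non-zero mean: (1-z)m + zm = m, a rise of z/(1-z).
- Zeros replaced by the overall mean: (1-z)m + z(1-z)m = (1-z)(1+z)m, a rise of z.

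| z | Rise, non-zero mean | Rise, overall mean |
|---|---|---|
| 20% | 0.2/0.8 = 25% | 20% |
| 40% | 0.4/0.6 = 67% | 40% |
| 50% | 0.5/0.5 = 100% | 50% |

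**2. Difference between two equal arms, zero shares differ, m = 100 in both.**

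| | 20% v 40% zeros | 20% v 50% zeros |
|---|---|---|
| Zeros kept | 80 v 60, difference 20 | 80 v 50, difference 30 |
| Non-zero mean | 100 v 100, difference 0 | 100 v 100, difference 0 |
| Pooled overall mean | 94 v 88, difference 6 | 93 v 82.5, difference 10.5 |
| Each arm's own overall mean | 96 v 84, difference 12 | 96 v 75, difference 21 |

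For example, with 20% v 50% the pooled overall mean is (80 + 50)/2 = 65, so control becomes 80 + 0.2 × 65 = 93 and support becomes 50 + 0.5 × 65 = 82.5.

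**3. Same comparison, zero shares equal (30% in each arm), non-zero means 100 v 70.**

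- Zeros kept: 70 v 49, difference 21, a 30% reduction.
- Pooled non-zero mean (85): 95.5 v 74.5, difference 21, a 22% reduction.
- Pooled overall mean (59.5): 87.85 v 66.85, difference 21, a 24% reduction.
- Arm-specific means: 100 v 70 (non-zero) or 91 v 63.7 (overall). The reduction stays at 30% and the absolute difference grows to 30 or 27.3.

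With equal zero shares and a pooled mean, then, only the relative difference shrinks.

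**4. Catastrophic-cost status.** Illustrative simulation of 400,000 households per arm: three lognormal cost categories (non-zero means 60, 60 and 160, log-SD 1), lognormal income (mean 1000, log-SD 0.8), threshold 20% of income, and replacement means pooled over arms.

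- Zero costs, 20% v 40% per category, no zero incomes: 53% v 40% catastrophic with zeros kept. Under the rule this becomes 68% v 71% (non-zero mean) or 65% v 65% (overall mean).
- Zero incomes in 10% of households, no zero costs: 69% with zeros kept, 64% to 65% under the rule.

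The two halves of the rule push in opposite directions, so the net bias depends on how many zeros of each kind occur.

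**The case against.** The strongest reply is that the authors may regard a recorded zero as non-response, which would explain why they put the word in quotation marks and handle it like a missing value. If zeros also counted toward the 10% exception, the rule would switch off before the shares used above are reached, and inflation would be capped at about 10% to 11% (z = 10%: 0.1/0.9 = 11%). The wording does not say this. The exception names missing data only, and no alternative is given for variables that exceed it. The ambiguity stands as something to resolve; it does not remove the stated rule. The cited sources and the full protocol may define when a zero is invalid, but they are not available here and the article's text makes no such distinction.

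It is also fair that the study-setting section lists travel, nutrition and lost income as real costs, and that the introduction reports that "catastrophic costs were experienced by 61% of TB-affected households". Free tests and medicines make zeros plausible for some items, not for total cost.

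Two stronger readings are tempting and are not supported.

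- A reader might infer that the rule erases part of any treatment effect. It does not: step 3 shows the absolute difference intact, or enlarged, when zero shares are equal. The article gives no zero shares and does not say that support would act by moving households to zero loss.
- A reader might infer that the definitive trial will be sized on these cost estimates. The article says only that the pilot will inform the design of a larger trial on catastrophic costs and TB outcomes, and an earlier estimate of 61% already exists.

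**Conclusion.** The point holds and should be fixed. As written, the plan overwrites true zeros on both sides of the 20% ratio. Mean costs in an affected category rise by z/(1-z) or by z, according to which mean is used. Catastrophic-cost status is misclassified upward through zero costs and downward through zero income. In the worked examples with unequal zero shares, the arm difference is lost completely with the non-zero mean and by 30% to 70% with a mean that includes zeros. The algebra needs no assumption beyond the rule; the sizes rest on assumed zero shares and, in step 4, on assumed distributions.

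The reach is limited. These outcomes are exploratory and unpowered, and feasibility and acceptability do not use patient costs. The point still matters because costs and catastrophic-cost proportions are tested across arms, and because the pilot is meant to inform a trial whose outcomes include catastrophic costs.

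**What to change.** Amend the cost-handling paragraph as follows.

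- Keep recorded zeros for direct expenses and lost income as valid values unless an entry is shown to be non-response.
- Impute only values that are truly missing. If mean replacement is kept for these, state whether the mean is pooled or by arm, confirm that zeros are included in it, and say what happens when more than 10% are missing.
- Do not replace a zero pre-TB annual income with a cohort mean. State how it enters the 20% ratio, for example through an income estimate based on the asset, housing and amenity data that the survey already collects, with a sensitivity analysis.
- Report the current rule only as a sensitivity analysis.

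The cost is one paragraph of analysis wording and the extra sensitivity analyses. No new data are needed, which matters because the study-status section puts the end of recruitment at September 2022. The downside is that headline costs become less directly comparable with the team's earlier work; running the current rule as a sensitivity analysis largely covers that.
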